### Data collection

The baseline questionnaire will be filled in during the intake appointment at the SSA, after signing informed consent. All other questionnaires will be filled in online, unless the participant prefers to receive a hard copy by postal mail.

Participants will receive questionnaires at baseline and after three, six, nine and twelve months.

In case questionnaires will not be returned within two weeks after the questionnaire is sent, the researcher will contact the participant by telephone to inform whether the participant has been able to complete the questionnaire and to ask the participant, if possible, to complete the questionnaire timely. In case the participant returns the questionnaire, but the received questionnaire is incomplete, the researcher will also contact the participant by telephone. The remaining questions will be repeated by the researcher, so that the questionnaire can be completed by the participant.

In addition to the questionnaires, after one year follow-up data regarding RTW, sickness absence, diagnosis, OHC interventions and investments made by the SSA will be obtained from the SSA database and the medical file of the worker at the SSA. These data will be checked with the self-reported information in the questionnaires.

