### Recruitment of participants

Workers without a permanent employment contract who have applied for a sickness benefit at the Dutch SSA and are sick-listed between one and two weeks, will receive an invitation package from the medical advisor of the SSA, on behalf of the researchers. It contains an invitational letter, a flyer with more details about the study, a consent form and a short questionnaire with a return envelope. A weekly query of the SSA database will be used for the recruitment of eligible workers.

The short screening questionnaire consists of six questions. The sick-listed worker will be asked to fill in whether he or she is interested to participate in the study and to indicate the day he or she applied for a sickness benefit. The Distress Screener, developed by van Oostrom and colleagues [30], will be used as a quick scan for early identification of distress, i.e. three questions of the Four-Dimensional Symptom Questionnaire (4DSQ) will be used to assess the degree of perceived mental health problems. Finally, the sick-listed worker will be asked whether he or she has ‘certainly not/probably not/maybe/probably/certainly’ the intention to RTW if health complaints are still experienced.

In case the sick-listed worker wants to participate and meets the eligibility criteria, he or she will be contacted by the researcher or research assistant for a first intake by telephone. During this intake more information about the study will be given. When the sick-listed worker has indicated to ‘maybe/probably/certainly’ have the intention to RTW despite health complaints, the sick-listed worker will be invited to participate in the RCT. Using the described exclusion criteria, the researcher or research assistant will decide whether the sick-listed worker is able to participate.

In case the sick-listed worker is able to participate, an intake appointment will be planned at the nearest participating front office of the SSA. During the intake, randomisation will be performed after signing informed consent and fulfilling the baseline questionnaire by the participant.

In Figure 1 the consecutive steps in the study design are summarized.

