#### Training of the professionals

Instruction will be given to all intervention teams by the researchers. At each participating SSA office instruction takes place by means of a presentation and role plays during one session of approximately three hours. In the beginning of this session all professionals will receive a syllabus with detailed information about the program, the protocol, practical summaries and schemes and practice material. A few months after the first participants have enrolled in the intervention, the researchers will visit every participating intervention team for a follow-up session to evaluate the first cases and to discuss difficulties in applying the protocol in daily practice.

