Quality of life (Euroqol)	X		X		X
ASE determinants (ASE questionnaire)	X		X		X
Work limitations (WLQ)			X		X
Health care utilization (Tic-P)	X	X	X	X	X
Patient satisfaction* (PSOHSQ)		X			

*Patient satisfaction with occupational health care services is only measured in the intervention group (as part of the process evaluation).

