### Blinding

The OHC professionals who perform the intervention cannot be blinded for the allocation of participants to the intervention group, because they will need to know when to apply the intervention. Also the OHC professionals who are not trained in the participatory supportive RTW program will be informed when a participant is allocated to their team for usual OHC. Randomisation of participants will take place on participant level and participants of both the control group and the intervention group will receive OHC by OHC professionals working at the same office. Therefore, blinding the professionals for the randomisation result is impossible.

Because participants need to be informed at least briefly about the content of usual OHC and the participatory supportive RTW program before they are able to sign an informed consent, they can as well not be blinded for the randomisation result. Also blinding the participants for the outcome measures will be impossible, as most of the outcomes are self-reported. Bias caused by a lack of blinding will however be limited for the measurement of the duration until first sustainable RTW, the primary outcome measure of this study, and the duration of the sickness absence period, as in addition to the questionnaires the SSA database will be used to measure these outcomes.

To guarantee blinded analyses of the collected data by the researcher, the data will be entered into a database by a research assistant using a unique research number for each participant.

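### Blank items on returned questionnaires are read out by telephone by the researcher, with nothing to keep the caller unaware of allocation: an avoidable risk of interviewer influence on the subjective secondary outcomes

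*Protocol article*

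**What the plan says.** Follow-up questionnaires at 3, 6, 9 and 12 months are self-completed, online by default and on paper if preferred (Data collection). A form that is not returned leads to a reminder call. A form that comes back with gaps is handled differently: "In case the participant returns the questionnaire, but the received questionnaire is incomplete, the researcher will also contact the participant by telephone", and then "The remaining questions will be repeated by the researcher, so that the questionnaire can be completed by the participant". The rule does not separate factual items from symptom, health or attitude scales.

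On the researchers' role, Training of the professionals says "Instruction will be given to all intervention teams by the researchers" and that, some months into enrolment, "the researchers will visit every participating intervention team for a follow-up session to evaluate the first cases".

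On masking, the Blinding section states that neither professionals nor participants can be blinded, and adds: "Also blinding the participants for the outcome measures will be impossible, as most of the outcomes are self-reported". Its one safeguard on the research side concerns the analysis: "To guarantee blinded analyses of the collected data by the researcher, the data will be entered into a database by a research assistant".

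**The concern.** A participant who left an item on mood, health or self-efficacy blank in private is asked to answer it aloud to a member of the research group. That group taught the programme to the intervention teams and discusses their cases. The participant knows the arm, and the caller may know it too. Spoken answers on such items can differ from private ones. If they differ more in one arm than in the other, the comparison of arms is biased.

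At stake are the self-reported secondary outcomes with no second source: 4DSQ, SF-36, EuroQol, ASE and WLQ. EuroQol also feeds the QALY difference in the cost-utility analysis. The article already accepts that participants are unblinded. Influence from the interviewer is a separate source of bias and, unlike the first, it can largely be avoided.

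**Working it through.** There is no figure in the plan to reproduce. The check sets the sections side by side.

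1. **Who asks.** Data collection names the researcher for the completion calls. Under Recruitment of participants the article does distinguish two roles: "he or she will be contacted by the researcher or research assistant for a first intake by telephone". The calls about blank items are given to the researcher alone.

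2. **Is the caller's group involved in the programme?** Yes. Training of the professionals gives the researchers both the instruction of the intervention teams and the review of their first cases. One section uses the singular and the other the plural. The text therefore supports saying that the caller comes from that group, but not that one individual does both.

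3. **Can the caller learn the allocation?** No provision prevents it, and there are several routes:
   - The 3-month form carries items for one arm only. The footnote to Table 1 reads "Patient satisfaction with occupational health care services is only measured in the intervention group". Anyone checking that form for gaps sees the arm, and could remember it at 6 and 12 months.
   - Every questionnaire asks about RTW coaching and about efforts such as contracting a rehabilitation agency (Prognostic measures). This is only suggestive, since coaching is part of usual care and agency contracts are listed as a general SSA investment.
   - The team visits discuss intervention cases.
   - The participant can simply mention it.

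4. **Does the coded data entry help?** It acts after collection. The call comes before it, with an identified participant. The role that is meant to analyse blind is also the role that hears these answers.

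5. **Which outcomes are exposed?** By Table 1, 4DSQ, SF-36, EuroQol, ASE and WLQ are collected after baseline at 6 and 12 months, so two waves are exposed. The baseline form is completed at intake before randomisation. Time to first sustainable RTW and sickness benefit duration are also taken from the SSA database.

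6. **Size.** Let p be the share of an outcome's answers obtained by call and d the mean shift from answering by telephone, in SD units, with I and C for the intervention and control arms. Then bias = p_I × d_I − p_C × d_C. It is zero when the two products are equal. The article gives neither p nor d. For scale only, assume an equal share of 10% to 30% in both arms and an arm-specific difference in shift of 0.2 to 0.5 SD:
   - low end: 0.10 × 0.2 = 0.02 SD
   - high end: 0.30 × 0.5 = 0.15 SD
   - participants per arm after the planned 20% loss: 86 × 0.8 = 68.8
   - standard error of a simple mean difference: sqrt(2/68.8) = 0.17 SD
   - ratio: 0.02/0.17 = 0.1 to 0.15/0.17 = 0.9 standard errors

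   The high end multiplies two pessimistic assumptions. The standard error ignores clustering and repeated measures. None of this is an estimate for this trial.

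**The case against.** The strongest reply is that telephone completion is a sensible defence against item missingness in a trial that expects 20% loss. The call covers only the gaps, and answers already given privately stand. The dominant bias in self-report, participants who know their arm, is disclosed under Blinding and again under Limitations of the study. Most of this stands. It limits the point to a marginal, avoidable addition and means that the calls need not be abandoned.

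Four stronger readings are tempting, and the article does not support them:

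- **The caller is known to be unblinded and to be the trainer.** Neither is stated. A research assistant performs the randomisation, and the caller's knowledge of the arm is an inference from the routes listed above.
- **Every incomplete form becomes an interview.** Only the unanswered items are repeated.
- **Satisfaction and ratings of SSA efforts bias the arm comparison.** Neither is a secondary outcome. The PSOHSQ is collected in one arm for the process evaluation, so it has no between-arm contrast to bias.
- **Calls are unscripted, the mode is unrecorded, or the online form lets items be skipped.** The article is silent on all three, and such detail may sit in working instructions. Silence is not evidence of absence.

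What the reply does not remove is the stated procedure: the researcher asks, for any item, with no masking described for the call.

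**Conclusion.** The point holds in a limited form. The article fixes a procedure in which the researcher, from the group that trains and reviews the intervention teams, collects blank items by telephone, subjective secondary outcomes included. The only research-side masking it describes protects the analysis and not the call. The result is an avoidable risk of interviewer influence on part of the 6- and 12-month self-report data.

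The size cannot be derived from the article. A bias arises only if there are enough blank items on returned forms and if answering by telephone shifts the two arms differently. With no arm-specific shift there is none. A reader might infer that the primary result is compromised. That is not supported, because sustainable RTW is also measured from the SSA database. This is a low-cost improvement and not a flaw that threatens the trial.

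**What to change.** Amend Data collection as follows:

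- Have the online form prompt for skipped items before submission, so that few calls are needed.
- Where a call is still needed, use a fixed script. Preferably give it to an existing team member who has no training or randomisation role and is not told the allocation. The research assistant who performs the randomisation would not qualify.
- Flag each item collected by telephone, and run a sensitivity analysis of the self-reported secondary outcomes and QALYs that excludes those answers.

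The cost is a setting in the online form, a short script and slightly more data-management work. Barring telephone completion of scale items altogether would exchange possible bias for more missing data, mainly among postal responders. That is a legitimate choice but is not required.

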### Sample size

Time to first sustainable RTW in a competitive job is the primary outcome measure for the power calculation. Based on a recent study on a participatory RTW intervention for temporary agency workers and unemployed workers with musculoskeletal disorders [22] a Hazard Ratio (HR) of 2.0 is assumed to be the minimal clinical and societal relevant ratio. This indicates that the participants in the intervention group RTW twice as quickly compared to the participants in the control group. Furthermore, it is assumed that a minimum of 2/3 of the participants will achieve first sustainable RTW during the first twelve months of the follow-up period [22]. Based on a power of (1-β=) 0.80 and a two-sided significance level of 0.05 (α) a sample size of 100 participants (n = 2 x 50) is needed. Next, potential clustering of cases guided by the same team of OHC professionals is taken into account. To correct for potential clustering of cases an ICC of 0.05 is used and the minimal number of teams is assessed: eight teams of OHC professionals who are trained in guidance according to the participatory supportive RTW program and eight teams of OHC professionals who deliver only usual OHC. Furthermore, based on comparable research [47], a loss to follow-up of 20% is expected. This results in a requisite number of 172 participants (n = 2 x 86).

### Randomisation procedure

Randomisation will take place on participant level. In line with previous research by Vermeulen et al. [21] pre-stratification of participants is based on information about type of worker before reporting sick, i.e. unemployed worker, temporary agency worker or fixed-term contract worker. To ensure an equal distribution of control group participants and intervention group participants in the three different SSA districts, participants will also be pre-stratified on district-level. Schemes with random permuted numbers will be used by the principal investigator to generate separate block randomisation tables with fixed block sizes of four.

Randomisation takes place during the intake appointment at the SSA office. After the informed consent form is signed and the baseline questionnaire is completed by the participant, the assistant of the SSA contacts the research assistant at the VU Medical Centre to perform the randomisation. The research assistant of the VU Medical Centre uses the block randomisation table of the correct stratum to determine the randomisation result. The participant will be informed immediately about the randomisation result, intervention or control group, and the consecutive steps. Participants who are allocated to the intervention group will be assigned to an intervention team of the corresponding SSA office for guidance according to the participatory supportive RTW program in combination with usual OHC. These intervention teams will not be involved in the guidance of control group participants. Control group participants will be assigned to a team of the corresponding SSA office that is not familiar with the intervention program.

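### Fixed blocks of four in an unblinded trial, with screening and table custody not described as separate, leave about a third of allocations predictable to anyone who sees a whole stratum

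*Protocol article*

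**What the plan says.** The Randomisation procedure section states: "Schemes with random permuted numbers will be used by the principal investigator" "to generate separate block randomisation tables with fixed block sizes of four". Participants are stratified by type of worker (three types) and by district (three). The Trial design section mentions only a separate table per district, so the number of strata is nine or three depending on which section is followed.

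Randomisation is done at the office intake. "After the informed consent form is signed and the baseline questionnaire is completed by the participant", an assistant at the agency office calls the university medical centre, where the research assistant "uses the block randomisation table of the correct stratum to determine the randomisation result". The participant hears the result straight away. On the professionals, the Blinding section says that "blinding the professionals for the randomisation result is impossible"; it also says that participants cannot be blinded.

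Entry is decided earlier. According to the Recruitment of participants section, a worker who is interested and appears eligible is telephoned: "he or she will be contacted by the researcher or research assistant for a first intake by telephone". The same section continues: "Using the described exclusion criteria, the researcher or research assistant will decide whether the sick-listed worker is able to participate". The office appointment is planned only after that.

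**The concern.** In an open trial the past allocations are visible. If every block has four places, two per arm, someone who has followed a stratum can work out the end of each block without seeing the table. Because the size is printed in the article, the rule itself is not hidden either.

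The eligibility decision and the use of the table are both given to a role called research assistant, and the principal investigator makes the tables. Someone who knows or suspects the next arm could admit, decline or reschedule a worker according to how good that worker's job prospects look. Such selection would feed directly into the hazard ratio for sustainable return to work. The Blinding section relies on the agency database to limit bias, but that protects the measurement of the outcome and not the choice of who enters at which point in the sequence.

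**Working it through.** **Inputs.** Block size 4, fixed; three worker types by three districts = 9 strata (Randomisation procedure), or 3 strata if only districts are used (Trial design); total 172, 1:1 (Sample size).

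**The plan's own figure.** The article gives no figure for predictability, so the number to reproduce is the total on which the counts rest.
- Schoenfeld's formula with HR 2.0, power 0.80 and two-sided 0.05 gives 66 events. 66 / (2/3) = 99, against the stated 100.
- Clustering with ICC 0.05 and 8 teams per arm: n = 50 × [1 + (n/8 − 1) × 0.05]. Solved, n = 50 × 0.95 / (1 − 50 × 0.05/8) = 47.5/0.6875 = 69.1 per arm.
- Loss of 20%: 69.1/0.8 = 86.4 per arm, matching 2 × 86 = 172.

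The sample size is not in dispute.

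**One complete block of four.** There are six equally likely orders. For an observer who knows the size and the earlier results:

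| Position | Chance that it is certain | Chance that the best guess is right |
|---|---|---|
| 1 | 0 | 1/2 |
| 2 | 0 | 2/3 |
| 3 | 1/3 (first two alike) | 1/3 × 1 + 2/3 × 1/2 = 2/3 |
| 4 | 1 | 1 |

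Certain: (1/3 + 1)/4 = 33.3%. Best guess: (1/2 + 2/3 + 2/3 + 1)/4 = 2.833/4 = 70.8%. Unpredictable allocation would give 0% and 50%.

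**Incomplete last blocks.** 172/9 = 19.1 per stratum. If the last block is equally likely to hold 0, 1, 2 or 3 participants, on average 1.5 fall in it and 17.6 in complete blocks. The incomplete part adds 1/12 of a certain allocation on average (1/3 when three places are filled, otherwise none). Certain per stratum: 17.6/3 + 1/12 = 5.95, and 5.95/19.1 = 31.2%.

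A simulation of 400 trials agrees. It places 172 participants at random over equally likely strata and draws block sizes with equal probability. The observer knows the set of sizes in use and all earlier allocations in the stratum:

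| Strata | Block sizes | Certain | Best guess right |
|---|---|---|---|
| 9 | 4 | 31.3% (54 of 172) | 69.8% |
| 9 | 4, 6 | 5.8% (10) | 68.3% |
| 9 | 4, 6, 8 | 2.3% (4) | 67.0% |
| 3 | 4 | 32.5% (56) | 70.6% |
| 3 | 4, 6, 8 | 2.4% (4) | 67.7% |

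Varying the sizes removes most of the certainty but little of the guessing advantage. It does nothing against someone who can read the table. The result hardly depends on whether there are nine strata or three.

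**The case against.** The strongest reply is that the article condenses a fuller protocol, and that custody of the list and division of tasks are commonly left to that document. A reader might infer that the person who screens also holds the table. The text does not support that: it shows the same role title in two places, not the same individual. Silence on custody alone would be no finding. What the article does fix is the block size, together with the role named on each side.

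Second, a real safeguard is already in place: allocation follows signed consent and the completed baseline questionnaire, through a call to a central site. This stands, and it makes manipulation at the moment of allocation difficult. It does not reach the earlier telephone decision or the scheduling of the intake.

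Third, the room for discretion is limited. Intention to return to work is a self-reported questionnaire item with a fixed cut-off, and the other criteria, such as a conflict with the agency or care already received, are largely factual. Some interpretation by telephone remains possible, but not much.

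Fourth, the percentages describe an observer who sees the whole stratum. Three districts share seven offices, so office staff generally see only part of a table, and they do not decide eligibility. Nor would a screener holding the table know the arm for certain: others may be randomised before the appointment, or the worker may not attend. It is therefore wrong to say that such a person knows every allocation when deciding eligibility.

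Last, one might say that no analysis could repair the bias. That is too absolute: the Statistical analysis section allows adjustment for baseline differences, which can reduce the measured part. Unmeasured prognosis would remain.

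**Conclusion.** The point holds as a risk of selection bias of moderate priority. As written, fixed blocks of four with open disclosure let an observer of a full stratum know about 31% of allocations for certain and guess about 70%, and the article describes no separation between those who decide entry and those who use the tables.

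The figures assume 1:1 blocks, equally likely strata and knowledge of all earlier allocations in the stratum. They are an upper guide for staff who see less, and the gap between telephone screening and office randomisation weakens them further. A reader might go on to infer that concealment has failed or that bias has occurred. The documents show neither.

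**What to change.** 1. Replace the fixed size of four with randomly varying sizes (for example 4, 6 and 8) within each stratum, and keep the sizes out of any document available to staff who recruit.
2. State that the tables are generated and held by existing staff who neither screen nor schedule participants. This is the essential part, because varying the sizes leaves best guesses at about 67%. If the roles are already separate, a sentence saying so is enough.
3. Keep the existing order of consent, baseline questionnaire and then central allocation; no change is needed there.

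The cost is a small change to how the tables are generated and a division of tasks among existing staff. The price is slightly more possible imbalance in small strata. The sample size is unaffected.
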